### Criteria for discontinuing or modifying allocated interventions {11b}

Given the minimal risks associated with receiving and discontinuing the intervention, providers are free to discontinue or modify the intervention as they saw fit (i.e., no pre-specified criteria necessary).

### Strategies to improve adherence to interventions {11c}

There are no strategies in the trial to improve adherence, as adherence is not a primary outcome of the study. However, to assess adherence to treatment, the *Therapist Adherence Rating Scale* (TARS) will be used.

### Relevant concomitant care permitted or prohibited during the trial {11d}

No contaminant care measures were taken as the trial was designed to assess the efficacy of the intervention in a real-world community setting.

### Provisions for post-trial care {30}

Given the minimal risk of harm for this study, provisions were not made for ancillary or post-trial care. Details about the Data Safety Monitoring Board can be found elsewhere in the manuscript.

### Outcomes {12}

Table 1 indicates which measures are primary and secondary outcome measures. See Table 2 for the timing of each measure. Participants will complete a consent form and demographics information (age, sex, etc.) in addition to the measures listed below.

**Table 1 Tab1:** Summary of descriptive, primary and secondary outcomes. Bolded Italics indicate primary outcomes in each domain

Domain	Measures
Descriptive & screening	Demographics; Adapted Brief Disability Questionnaire; Montreal Cognitive Assessment; PROMIS-SD; WHODAS 2.0; Screen for sleep disorders (SCISD, ESS, WatchPAT)
Fidelity	Provider-Rated TranS-C Checklist; Memory Support Treatment Provider Checklist
Adverse Events	Adverse events checklist
**Aim 1**	
Sleep and Circadian Functioning	***PROMIS-SD*** **;** PROMIS-SRI; Sleep Health Composite Score; Sleep Diary (mean sleep efficiency [total sleep time/time in bed X 100]; total wake time (TWT), and total sleep time (TST); Actigraphy (mean TWT, TST, daytime activity)
Daytime Functioning	***Sheehan Disability Scale;*** WHODAS 2.0; ESS
Well-being	***Satisfaction with Life Scale;*** PANAS
**Aim 2**	
Mediators: Patient Memory	Patient Treatment Recall Task (Cumulative recall); Thoughts and Applications Task
**Aim 3**	
Moderators	Demographics (age, education); Montreal Cognitive Assessment; Cognitive Failures Questionnaire; PROMIS-SD/SRI
**Exploratory Aims**	
Adherence	TARS
Credibility	Credibility and Expectancy Questionnaire
Utilization	Utilization Scale
Acceptability, Appropriateness, Feasibility	Acceptability of Intervention Measure; Appropriateness Intervention Measure; Feasibility of Intervention Measure
**Manipulation Checks**	
Memory Support	Memory Support Rating Scale (Total amount; Number of types)
Patient Memory	Patient Treatment Recall Task

*PROMIS-SD* PROMIS-Sleep Disturbance, *WHODAS 2.0* World Health Organization Disability Assessment Schedule, *PANAS SCISD* Structured Clinical Interview for Sleep Disorders, *ESS* Epworth Sleepiness Scale, *PROMIS-SRI* PROMIS-Sleep Related Impairment, *PANAS* Positive Affect and Negative Affect Schedule, *TARS* Therapist Adherence Rating Scale

**Table 2 Tab2:** SPIRIT depiction of tPliming of study measures

	**Screen**	**Pre-Tx**	**Tx Sessions**				**Post-Tx**	**6FU**	**12FU**
			**1–3**	**4**	**5–7**	**8**			
**Patient**									
Demographic Form	x								
Adapted Brief Disability Questionnaire	x								
Montreal Cognitive Assessment	x								
SCISD^a^	x	x							
WatchPAT	x								
Additional Eligibility Items	x								
PROMIS-SD	x	x					x	x	x
PROMIS-SRI		x					x	x	x
Sleep Health Composite		x					x	x	x
Sleep Diary		x					x	x	x
Actigraphy		x					x		
Sheehan Disability Scale		x					x	x	x
WHODAS 2.0	x	x					x	x	x
Epworth Sleepiness Scale	x	x					x	x	x
Satisfaction with Life Scale		x					x	x	x
PANAS		x					x	x	x
Patient Treatment Recall Task				x			x	x	x
Thoughts and Applications Task				x			x	x	x
Cognitive Failure Questionnaire		x					x	x	x
Credibility and Expectancy			x						
Utilization Scale		x					x	x	x
Adverse Events Checklist							x		
**Therapist**									
Patient Adherence via the TARS			x	x	x	x			
Acceptability, appropriateness, feasibility						x			
Provider-rated TranS-C Checklist			x	x	x	x			
Memory Support Treatment Provider Checklist			x	x	x	x			
**UC Berkeley Team**									
Memory Support Rating Scale	Based on power analysis, one treatment tape per patient will be randomly selected for coding								
TranS-C Fidelity Checklist	Checklist of treatment elements specific to TranS-C will be applied to 10% of tapes								

Additional Eligibility Items include measures for determining inclusion criteria: low-income and exclusion criteria: night shift work, substance use/dependence, current suicide risk, homelessness, and certain medical conditions.

*SCISD* Structured Clinical Interview for Sleep Disorders, *PROMIS-SD* PROMIS-Sleep Disturbance, *PROMIS-SRI* PROMIS-Sleep Related Impairment, *WHODAS 2.0* World Health Organization Disability Assessment Schedule, *PANAS* Positive Affect and Negative Affect Schedule, *TARS* Therapist Adherence Rating Scale, *TranS-C *Transdiagnostic Intervention for Sleep and Circadian Dysfunction.

^a^At screening, the SCISD was used to assess hypersomnolence, narcolepsy, obstructive sleep apnea, and REM sleep behavior disorder. At pre-treatment the SCISD was used to collect diagnostic information pertaining to the presence of the following sleep disorders: insomnia, circadian rhythm sleep–wake disorders, restless leg syndrome, nightmare disorder, and non-REM sleep arousal disorder: sleepwalking and sleep terror types

### Participant measures

Across participant measures, the post-treatment time point is of primary interest.

#### Sleep and circadian functioning

Sleep and circadian functioning will be measured using a multi-method approach employing global, subjective (daily sleep diary), and objective (actigraphy) indices.

The *PROMIS Sleep Disturbance Scale* (PROMIS-SD) is an 8-item scale that will be used to assess perceived sleep problems (e.g., sleep quality, perception of sleep difficulties) over a 7-day period [85]. Items are rated on a 5-point scale ranging from 1 (not at all) to 5 (very much). Sleep disturbance will be measured at each assessment point (pre-treatment, post-treatment, 6FU, and 12FU). T-scores will be calculated from the sum of raw scores using treatment manuals for each timepoint. Higher scores indicate greater sleep disturbance. This scale has demonstrated moderate reliability and validity [85].

The *PROMIS Sleep Impairment Scale* (PROMIS-SRI) is an 8-item scale that will be used to assess perceived sleep problems during waking hours (e.g., alertness, sleepiness, tiredness) over a 7-day period [111]. Sleep impairment will be measured at each assessment point. Items are scored on a 5-point scale ranging from 1 (not at all) to 5 (very much). Higher scores indicate more sleep-related impairment. T-scores will be calculated from the sum of raw scores using treatment manuals for each time point.

The *Composite Sleep Health Score* (CSHS) will be used to calculate a cumulative score that indicates how well someone sleeps. CSHS will be measured at each assessment point. It is comprised of the sum of scores on 6 sleep health dimensions: regularity (midpoint fluctuation), satisfaction (sleep quality question on PROMIS-SD scale), alertness (daytime sleepiness question on PROMIS-SRI scale), timing (mean midpoint), efficiency (sleep efficiency), and duration (total sleep time) [112]. The satisfaction and alertness dimensions are drawn from questions on the PROMIS-SD and PROMIS-SRI scales respectively. All other dimensions are drawn from the daily sleep diary. Each dimension is dichotomized as either 0 = poor or 1 = good. For each dichotomized dimension, we will derive cut-off points for each dimension based on empirical literature and/or recommendations/consensus. Total sum scores range from 0 to 6, where higher scores indicate better sleep health.

The *Consensus Sleep Diary* (CSD) [113] will be used to track subjective sleep for 7 days at each assessment point. The CSD was modified such that the question assessing perceived sleep quality was removed and a question assessing napping time was added (“Did you nap yesterday, if so for how long?”). Daily sleep diaries have been demonstrated to yield a reliable and valid clinical index of sleep and circadian function [114, 115]*.* From the Daily Sleep Diary, mean sleep efficiency (total sleep time/time in bed X 100), total wake time (TWT), and total sleep time (TST) will be calculated.

*Actigraphy* will be used to assess sleep–wake and activity patterns for 7 days at pre-treatment and post-treatment. Participants will wear an ActiGraph wGT3X-BT® (ActiGraph, LLC) which samples movement every 60 s. For actigraphy, mean TWT, TST, and daytime activity will be calculated.

#### Daytime functioning

Three measures will be administered to assess daytime functioning, which are measured at each assessment point. First, the *Sheehan Disability Scale* (SDS) will be used to assess impairment in work/school, social, and family life [116]. Items are rated on a scale of 0 (not at all) to 10 (extremely). Items are summed to produce a single score. Scores range from 0 to 30, with higher scores indicating higher functional impairment. This scale has demonstrated good reliability and validity [116, 117]. Second, the *World Health Organization Disability Assessment. Schedule* (WHODAS 2.0) is a 36-item scale that will be used to assess difficulty in specific areas of functioning during the past 30 days [83]. Items are scored on a 5-point scale from 1 (none) to 5 (extreme or cannot do). Items are summed to produce a single score. Scores range from 36 to 180, with higher scores indicate greater disability. The WHODAS 2.0 has excellent reliability and validity [83, 118]. Third, the *Epworth Sleepiness Scale* (ESS) is an 8-item scale that will be used to measure excessive daytime sleepiness by assessing the likelihood of falling asleep in different situations [88]. Items are scored on a 4-point scale from 0 (would never doze) to 3 (high chance of dozing) and are summed to produce a single score. Scores range from 0 to 24, with scores over 10 reflecting excessive daytime sleepiness.

#### Well-being

Well-being will be assessed with two separate measures, which are assessed at each assessment point. First, the *Satisfaction with Life Scale* (SWLS) is a 5-item instrument that will be used to measure of global satisfaction with one’s life [119]. Items are scored on a 7-point scale ranging from 1 (strongly disagree) to 7 (strongly agree). Items will be summed to produce a single score. Scores range from 5 to 35, with higher scores indicating higher levels of perceived satisfaction with life. The SWLS scale has been found to have excellent reliability and validity [119]. Second, the *Positive Affect and Negative Affect Schedule* (PANAS) will be used to measure emotion and mood [120]. The scale consists of 20 items, with 10 items measuring positive affect (e.g., excited, enthusiastic) and 10 measuring negative affect (e.g., irritable, scared). Items are scored on a 5-point scale ranging from 1 (very slightly or not at all) to 5 (extremely). Items will be summed to produce a single score for positive and negative affect. Scores can range from 10 to 50 for both Positive and Negative Affect, with higher scores representing higher levels of either Positive or Negative affect.

#### Memory assessments

Memory will be assessed using the Patient Treatment Recall Task and the Thoughts and Application Task at mid-treatment (between sessions 4 and 5), post-treatment, 6FU, and 12FU.

The *Patient Treatment Recall Task* will be used to assess participant memory for treatment contents [3]. Participants are required to spend a minimum of 5 min on the recall task and are given up to a maximum of 10 min to recall as many distinct treatment points as possible from all the sessions that they have attended so far (cumulative recall). This task has excellent interrater reliability and, in previous studies, is associated with the amount of memory support received [3, 121]. The overall number of treatment points recalled is determined using a scoring rubric developed in a previous study [3]. The number of treatment points will be summed at each measurement points to produce a single score.

To further assess participant memory and learning, an adapted version of the *Thoughts and Application Task* will be used [122]. The *Thoughts Task* assesses how often participants *thought* about therapy points learned from treatment in the past 24 h. Participants are asked: “In the last 24 h, have the contents covered in your sleep coaching sessions to date come to mind?”, if participants answer no, they are prompted to think for at least 1 min to see if any content comes to mind. If participants answer yes, they are asked “If you were to put a number to it, how many times did the contents covered in your sleep treatment sessions come to mind in the past 24 h?”. Participants are instructed to “write down what contents from treatment came to mind within the last 24 h”. Participants are given a minimum of 1 min and a maximum of 6 min for this task. Similarly, in the *Applications Task* participants are asked if they *applied* any of the treatment points that they learned from the previous sessions in the past 24 h: “In the past 24 h, did you get to apply any of the contents covered in your therapy sessions or use the skills you have been learning during therapy?”, if a participant answers no, they are prompted to think for at least 1 min to see if any content they applied comes to mind. If participants answer yes, they are asked, “If you were to put a number to it, how many times did you apply the contents covered in your sleep treatment sessions in the past 24 h?”. Participants are then instructed to “write down what contents from treatment you were able to apply within the last 24 h”, participants are given a minimum of 1 min and a maximum of 6 min for this task to write down content they have applied in the last 24 h. The overall number of treatment points from the thoughts and applications task will be coded using the same manual as the *Patient Treatment Recall Task.* Number of treatment points from the Thoughts and Applications will be summed separately for each task.

#### Cognitive functioning

The *Cognitive Failures Questionnaire* (CFQ) will be used to assess cognitive functioning at each assessment point. The CFQ is a 25-item scale that specifically assesses failures in perception, memory, and motor function [123]*.* Items are scored on a 5-point scale from 0 (never) to 4 (very often). Items are summed to produce a single score. Scores range from 0 to 100, with higher scores indicating greater cognitive failures.

### Participant exploratory measures

#### Credibility

An adaptation of the *Credibility Expectancy Questionnaire* (CEQ) will be used to assess participants’ perceptions of treatment credibility and outcome expectancy [124]. The CEQ will be measured after treatment session 2. Specifically, the 6-item CEQ was adapted to include only the first four items, assessing the credibility factor fully and the first item of the expectancy factor. In total, four items will be rated via a combination of three 9-point scales (1 = not at all logical/not at all successful/not at all confident, 9 = very logical/very successful/very confident) and one 0–100% scale. Scores from all items will be converted to standardized *z*-scores, and then a total sum CEQ score will be derived, in addition to separate sum scores for the credibility and expectancy factors. Higher scores indicate higher perceived treatment credibility and expected improvement.

#### Utilization

The *Adapted Utilization Scale* will be administered to assess how often sleep health behaviors are performed from TranS-C. The Utilization Scale will be measured at each assessment point. The *Utilization Scale* [125] was modified to address sleep health behaviors relevant to the participants in this study, and to simplify overly complex items, resulting in a 19-item scale. Each sleep behavior is rated on a 5-point scale from 0 (I never use it) to 4 (I always use it). A Total Utilization Treatment Score was created by calculating the mean of all 19 items on the scale at each timepoint separately. Higher scores indicate greater utilization of sleep behaviors learned in treatment.

### Other participant measures

#### Adverse events

The method for assessing adverse events (AEs) follows prior research [126, 127]. A trained assessor will administer the adverse events checklist to clients to assess possible AEs at the post-treatment assessment. *Examples of the questions to be asked are:* I’m going to go through a list of symptoms please let me know whether the sleep changes you made during the sleep coaching treatment that interfered with your normal functioning in anyway? Is the [negative effect] still present? What makes you think that [negative effect] was related to a treatment you received in this study? Then the participant is asked to rate the frequency, intensity and interference caused by the [negative effect] for the past week. Examples of symptoms assessed include low mood, extreme sleepiness, and worsening sleep.

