## Introduction

### Background and rationale {6a}

Patient memory for the content of treatment is poor. Only one third of recommendations made during physician visits are accurately recalled (e.g., [1–3]), and patients may recall *in*accurate information. Indeed, one study found that 25% of patients recalled treatment recommendations that had *not* been made [4]. Patients receiving cognitive and behavioral treatments have similarly poor memory for their treatment [3, 5]. Collectively, these findings are important because poor memory for treatment has been associated with poorer adherence [6–8] and poorer outcomes [3, 7, 9].

There are several explanations for why patient memory may be poor. First, even when memory is functioning optimally, memory can fail during the encoding and retrieval process [10]. Second, cognitive and behavioral treatment sessions are long, cover complex material, and can elicit negative emotions that bias attention and in turn bias encoding of information [11]. Third, patients may also struggle to transfer knowledge learned in therapy to real-world situations, known as the transfer of learning problem; in other words, they may struggle to recall applicable treatment skills and concepts in their everyday lives [12].

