### Adverse event reporting and harms {22}

In this trial, adverse events (AEs) and serious adverse events (SAEs) are not expected and there is no biological plausibility for this intervention to cause any NIH-defined serious events such as hospitalizations, deaths, or disability. However, these events can occur within the trial population, but they are not anticipated to be related to the trial. Potential harms of treatment may arise from the sleep restriction and stimulus control components of TranS-C, which have been associated with a small amount of short-term sleep deprivation, increased sleepiness, and a deterioration in functioning [155, 156]. Actigraphy can cause minor skin irritation from the watch band, but this is rare. WatchPAT, which screens for sleep apnea, may cause transient psychological distress in some participants, but this is rare. The method for assessing adverse events (AEs) follows prior research [126, 127]. A trained assessor will administer a checklist to patients to systematically assess for possible AEs at the post-treatment assessment. The checklist will screen for unwanted symptoms following treatment and for each endorsed symptom several follow-up questions will be asked (for details, see “Adverse events checklist” under Outcomes). Furthermore, adverse events related to treatment will be assessed by therapists non-systematically throughout treatment. SAEs that are unexpected will be reported to the IRB, NIA program officer, and to the independent DSMB within 48 h of the study’s knowledge of the SAE. All AEs will be reported in future publications, including their nature, severity (mild, moderate, severe), and the relationship to the trial (related, not related).

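### The one systematic adverse-event checklist comes at post-treatment with past-week ratings, so the short-term harms the protocol names get no described rating for when they occurred

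*Protocol article*

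**What the plan says.** The harms section (Adverse event reporting and harms {22}) describes one systematic assessment: "A trained assessor will administer a checklist to patients to systematically assess for possible AEs at the post-treatment assessment". The description of the measure under Other participant measures agrees: "A trained assessor will administer the adverse events checklist to clients to assess possible AEs at the post-treatment assessment". In Table 2 the row "Adverse Events Checklist" has a single mark, consistent with the post-treatment column and with nothing at the sessions or the follow-ups.

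The occurrence question in the measure description asks "whether the sleep changes you made during the sleep coaching treatment that interfered with your normal functioning in anyway". A further question asks whether the effect persists. After that, "the participant is asked to rate the frequency, intensity and interference caused by the [negative effect] for the past week".

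The harms section says adverse events are not expected. It then names potential harms from the sleep restriction and stimulus control components, "which have been associated with a small amount of short-term sleep deprivation, increased sleepiness, and a deterioration in functioning". It commits to publishing the nature, severity (three grades) and relatedness of all adverse events. For the treatment period itself it adds that "adverse events related to treatment will be assessed by therapists non-systematically throughout treatment".

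**The concern.** The instrument and the harm do not match in time. The named harms are short-lived and arise while the patient is applying techniques taught during treatment. The only structured measurement comes after treatment has ended, and its frequency, intensity and interference ratings look back one week. An effect that was troublesome in the middle of treatment and has since settled would be reported from memory and then rated for a week in which it may be absent.

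At stake is the harms report, not the efficacy analysis. Participants are aged 50 or over and have mobility impairment, so a period of marked sleepiness or poorer functioning is worth measuring properly even when it passes. The protocol also undertakes to publish severity, and the instrument as described does not supply it for a resolved effect.

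**Working it through.** The protocol states no figure for this point, so there is none to reproduce. The check is timing arithmetic followed by a comparison of sections.

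**Inputs**
- Treatment length: 8–10 weeks (Explanation for the choice of comparators {6b}).
- Lag from final session to post-treatment assessment: 0–2 weeks (Plans for assessment and collection of outcomes {18a}).
- Rating window: 1 week (Adverse events).

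**Formulas**
- Interval from treatment start to checklist = treatment weeks + lag weeks.
- Share covered by the rating = 1 / interval.
- Treatment weeks inside the window = max(0, 1 − lag).

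| Treatment (weeks) | Lag (weeks) | Interval (weeks) | Share covered | Treatment weeks in window |
|---|---|---|---|---|
| 8 | 0 | 8 | 12.5% | 1 of 8 |
| 8 | 1 | 9 | 11.1% | 0 of 8 |
| 8 | 2 | 10 | 10.0% | 0 of 8 |
| 10 | 0 | 10 | 10.0% | 1 of 10 |
| 10 | 1 | 11 | 9.1% | 0 of 10 |
| 10 | 2 | 12 | 8.3% | 0 of 10 |

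The window therefore covers 8.3% to 12.5% of the interval, and at best the last treatment week.

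**What happens to a resolved effect**
1. Occurrence: the question reaches back over treatment, so the effect can be endorsed, by recall over up to about 12 weeks.
2. Persistence: it can be recorded as no longer present.
3. Frequency, intensity and interference: these are asked for the past week only, so they describe a period after the effect resolved.
4. Intensity when it occurred: no described item asks for it.

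**Whether the therapist route fills the gap**
The protocol itself calls this route non-systematic. Under Treatment fidelity, each therapist is allocated to one arm only, so any difference in how readily therapists notice or record events is inseparable from arm. It can add individual reports but cannot replace a structured rating.

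**The case against.** Several counter-arguments have force.

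- **Resolved harms are not lost.** A reader might infer that they go unseen. The documents do not support that, because the occurrence and persistence questions let them be recorded. What is missing is their rating, and their detection rests on recall.
- **The full checklist is not shown.** The article gives examples of the questions and refers to earlier research for the method. It also does not say that the past-week ratings are the source of the published severity grade. This stands as a caution: if the complete instrument has a worst-intensity item, stating it would settle the rating part. The single timing is fixed in three places and would remain.
- **The harms are described as minor.** Adverse events are said not to be expected, and the effects are potential and small. This limits the importance of the point. It does not explain a rating window that misses the effects named.
- **The timing of the techniques is not given.** Sleep restriction and stimulus control belong to Core module 2, but no session is stated. That an effect has passed by post-treatment is likely, not certain.
- **Other safeguards exist.** Weekly sessions, recorded sessions, supervision, expedited reporting of unexpected serious events and a monitoring board all help with serious problems. None gives a structured rating of a transient, non-serious effect.

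A stronger reading is also tempting: that the harms comparison is biased because one arm is trained to remember better. The Background section says the intervention targets memory for treatment contents and not general memory, and remembering that one was sleepy is not recalling a treatment point. The Background statement "Only one third of recommendations made during physician visits are accurately recalled" concerns medical advice and cannot be carried over to symptoms. The checklist does tie effects to changes made in treatment, so a difference in recall by arm is possible. Its existence, size and direction are unknown, and no risk ratio can be derived from the documents. The statistical methods sections also state no between-arm test of harms.

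**Conclusion.** The point holds as a measurement weakness. The only systematic instrument is given once, and its described ratings cover about 8–12% of the 8–12 weeks since treatment start, with no treatment week covered once the lag reaches one week. For the short-term effects the protocol names, occurrence depends on recall and intensity at the time is not rated, although severity is promised for all adverse events. Non-systematic therapist capture, nested within arm, does not repair this.

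The conclusion rests on the stated treatment length and lag, and on the questions shown being representative of the checklist. It needs no assumption about event rates or about recall by arm. The primary efficacy analyses are unaffected. The change is worth making because harms reporting improves at little cost.

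**What to change.** 1. At post-treatment, keep the past-week rating and add, for each endorsed effect, a rating at its worst since the previous adverse-event contact, or since treatment start where there was none.
2. Give the same checklist, with the same two ratings, at the assessor contact that already takes place between sessions 4 and 5. The Blinding section states that assessors are masked. If sessions are evenly spaced, this contact falls at about week 4–5 (half of 8–10 weeks), and the longest recall drops from 12 weeks to about 7 (12 − 5).
3. At both contacts, administer the checklist after the Patient Treatment Recall Task and the Thoughts and Applications Task. Those tasks supply the Aim 2 mediator, and questions about sleep changes made in treatment could otherwise cue recall.
4. Report the assessor data by arm, and list therapist-noted events separately.

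The cost is a few minutes on calls already scheduled and one extra rating per endorsed effect. Participants already past mid-treatment when the change is made will have only the post-treatment checklist, so the report should state how many contributed one contact and how many two.
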